#### Objective 4: Prospective single-arm intervention trial

By designing and adapting HCV treatment workflows for each specific clinical site and training frontline healthcare providers, we hypothesize that we can effectively treat HCV across multiple primary care clinics serving vulnerable, high-risk populations. We plan to enroll 289 patients over 6 months. Following the baseline assessment, design of the site-specific HCV treatment workflows, and training of frontline healthcare providers, we will implement the workflows across our seven clinical sites and measure both clinical and implementation outcomes. The SPIRIT figure shows the timeline of enrollment, intervention, and assessments for the trial (Table 2). The SPIRIT checklist is provided in Additional file 1.

**Table 2 Tab2:** Erase Hep C study SPIRIT figure

	Screen	Enrollment	Treatment				
			Start	End (Glecaprevir / Pibrentasvir)	End (Sofosbuvir / Velpatasvir)	SVR12 (Glecaprevir / Pibrentasvir)	SVR12 (Sofosburvir / Velpatasvir)
Timepoint	***T***_**-1**_	***T***_**0**_	***T***_**1**_** = up to 90 days after *****T***_**0**_	***T***_**2**_** = *****T***_**1**_** + 60 days**	***T***_**3**_** = *****T***_**1**_** + 90 days**	***T***_**4**_** = *****T***_**2**_** + (90–120 days)**	***T***_**5**_** = *****T***_**3**_** + (90–120 days)**
ENROLLMENT:							
Eligibility Screen	X						
Informed Consent		X					
Interview		X		X	X		
Obtain EMR Data	X	X	X	X	X	X	X
INTERVENTION:							
Implement Site-Specific HCV Treatment Workflows		X	X	X	X	X	X
ASSESSMENTS:							
Demographic Variables		X		X	X		
Socioeconomic Variables		X		X	X		
Substance Use Variables		X		X	X		
Sexual Behavior Variables				X	X		
Medical History		X		X	X		
Labs	X	X		X	X		
SVR12						X	X
2º Clinical Outcomes			X	X	X	X	X
2º Implementation Outcomes			X	X	X	X	X

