#### Enrollment

Study participants will be enrolled over a 6-month period. Study participants will interact with the research team at one or two time points: upon enrollment and, among those who go on treatment, at the end of treatment completion, which may be approximately 2–3 months from enrollment.

At the time of the patient’s clinic visit, a member of the research team will meet with the patient to describe the study and obtain written informed consent from those willing to participate. Clinic staff will provide an introduction of the eligible patient to the research team, as needed. Research team members will also recruit pre-screened patients from around the clinic setting with the help of clinic staff. The team will work with clinic staff to position themselves within the clinics so as to minimize disruption of workflows and clinical care.

On a biweekly basis, the research team will examine study progress by reviewing enrollment at each study site, including basic demographics of study participants, to ensure enrollment is occurring as intended. The research assistant and research coordinator will monitor study progress weekly. Additionally, we will track reasons why study participants were not treated using the site-specific HCV treatment workflows (e.g., changes in clinical status, lost to follow-up from the clinic). We will also generate estimates of how many study participants are at each step along the HCV care cascade. There will be specific thresholds to trigger an ad hoc review if enrollment is not occurring as intended.

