#### Second interview at treatment completion

Regimens typically require 8 or 12 weeks of treatment. Upon treatment completion, a laboratory test is performed to measure HCV viral load. This test is repeated 12 weeks after treatment completion (SVR12) to ensure that the response is sustained and the patient is cured of HCV. A viral load < 15 IU/mL is considered undetectable. Record of a laboratory test taken at the time of treatment completion will serve as a proxy for treatment completion. The second, shorter interview will ideally occur when the participants have their blood drawn for this test at treatment completion. Follow-up data will be collected on substance use and sexual behavior during treatment, medication adherence, and treatment side effects. If needed, research team members may reach out to the study participant by phone to arrange a time to meet for the second interview.

In the absence of test results, other markers for treatment completion may be used. These include self-report, date of last bottle pickup + 28 days, or clinical documentation of treatment completion in a note in the EMR. Study participants who do not pick up all treatment doses or do not return for a final laboratory test for viral load will be considered lost to follow-up and will be assumed to have not achieved SVR12.

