### Sample size justification

We predict that we will achieve SVR12 in 75% of patients enrolled in our study. We will use the “intention-to-treat” principle by including those enrolled in the study and lost to follow-up in the denominator. Therefore, the denominator will consist of the population of patients at participating clinical sites who have been screened and diagnosed with chronic HCV infection and who have provided informed consent to participate in our study, regardless of whether treatment was initiated or not. These estimates were based on experience treating HCV in this patient population, as well as three published studies of HCV treatment interventions for people experiencing homelessness in the primary care setting [9, 10, 21].

With the expectation that 75% of patients enrolled in the study will achieve SVR12, a two-sided 95% confidence interval will be constructed with a half-width no more than 5% from the point estimate. In order to assure with 95% confidence that the true proportion achieving SVR12 under the locally contextualized site-specific HCV treatment workflows is within 5% of the observed proportion, the required sample size is 289 patients (Fig. 2).

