### Analytical approach

We will quantify the proportion of the study population with HCV that achieved SVR12, including a confidence interval for this proportion, using the “intention-to-treat” principle as detailed above. Secondary analyses will follow the “per-protocol” approach where the denominator will exclude participants lost to follow-up.

Participants who do not pick up all their HCV medication and who do not complete a final laboratory test for viral load by the end of the trial period will be recorded as not having completed treatment, considered lost to follow-up, and assumed to have not achieved SVR12. Participants who either miss or delay treatment doses or who do not pick up all treatment doses, but return for a treatment completion lab or SVR12, will be retained within the dataset and recorded as non-adherent for descriptive analyses. We will also evaluate the number and proportion of patients moving through each step of the HCV care cascade, from diagnosis of HCV and enrollment to achieving SVR12 in order to better understand barriers within the care cascade. General reasons for failure to initiate and complete treatment will be discussed with clinic staff and summarized, as will delays between each step of the care cascade.

To derive proportions and 95% confidence intervals (95% CI), we will apply generalized estimating equations (GEE) to logistic regression models without predictors and interpret the anti-logit of the intercept as our proportion. Bias-corrected GEE will be applied to account for a small sample size. We will examine characteristics of the patient population stratified by achievement of SVR12. These characteristics will include age, sex, race, ethnicity, housing factors, education, employment status, payor, mental health conditions and psychiatric diagnoses, substance use history, sexual behavior, medical comorbidities, clinical site, and adherence to HCV treatment. These characteristics will also be evaluated after adjusting for covariates using a multivariable logistic regression model. Reported outcomes will include adjusted odds ratios for SVR12 and their 95% confidence intervals. We will use GEE models to account for clustered data and correct for small sample size, as described above. We will also conduct similar exploratory analyses for our secondary outcomes.

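### The adjusted SVR12 model lists two on-treatment variables, sexual behavior and adherence, that never-treated participants cannot have, although those participants count as failures

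*Protocol article*

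**What the plan says.** The Analytical approach section names 14 patient characteristics to be tabulated by SVR12 status. The list ends with "sexual behavior, medical comorbidities, clinical site, and adherence to HCV treatment". The section then states: "These characteristics will also be evaluated after adjusting for covariates using a multivariable logistic regression model". Adjusted odds ratios for SVR12 with 95% confidence intervals are to be reported, and similar exploratory analyses are planned for the secondary outcomes.

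The data schedule is set elsewhere in the protocol article:

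- Under Enrollment, the research team meets participants "upon enrollment and, among those who go on treatment, at the end of treatment completion".
- The topics listed for the first interview do not include sexual behavior.
- Under Second interview at treatment completion: "Follow-up data will be collected on substance use and sexual behavior during treatment, medication adherence, and treatment side effects".
- In Table 2 (the SPIRIT figure), the row "Sexual Behavior Variables" is marked only in the two end-of-treatment columns.
- Under Data collection, medication pickup dates are extracted from the medical record, and the first pickup stands in for the start of treatment.

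The Sample size justification puts every consented participant in the SVR12 denominator, whether or not treatment began.

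**The concern.** The covariate list conflicts with the protocol's own data schedule. For a participant who never starts treatment, sexual behavior during treatment and adherence to treatment are undefined. They are not values that exist and went unrecorded, so a missing-data rule in an analysis plan would not repair the model. Imputation would assign values to something that never happened.

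The choice also affects what the odds ratios mean. The Discussion presents the all-consented denominator as the study's advance over earlier studies limited to patients who began treatment. A model that needs these two variables moves back toward that narrower population, while its output could still be read as describing all enrollees.

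Adherence raises a second problem. It arises after enrollment and plausibly lies on the path from housing, substance use or clinic to cure. Holding it fixed removes whatever those factors do through it.

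**Working it through.** **The plan's own figure.** The protocol predicts: "We predict that we will achieve SVR12 in 75% of patients enrolled in our study". It asks for "a two-sided 95% confidence interval will be constructed with a half-width no more than 5% from the point estimate" and concludes that "the required sample size is 289 patients". The Wald formula gives n = 1.96² × 0.75 × 0.25 / 0.05² = 288.1, rounded up to 289, with a half-width of 0.0499 at that size. The sample size reproduces and is not in dispute.

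**Expected outcomes.** 0.75 × 289 = 216.75, so about 217 cures and 289 − 217 = 72 failures.

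**Failures that can have second-interview data.** There are two sources:

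- Virological failures. Let c be the cure rate among those tested for SVR12. The number is 217/c − 217. The Abstract credits the simplified algorithm with a cure rate above 97%. Taking c = 0.97 gives 223.7 − 217 = 6.7.
- Participants interviewed at treatment completion who then miss the SVR12 test. Call this L. The documents give no figure, so L is assumed and varied.

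The calculation also assumes that every completer is interviewed, that nobody who stops early is interviewed, and that the fit uses only participants with the values.

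| L, as % of 289 (assumed) | Failures with data | Failures excluded | Share of 72 excluded | SVR12 in fitted set |
|---|---|---|---|---|
| 0% | 6.7 | 65.3 | 91% | 97% |
| 2% (5.8) | 12.5 | 59.5 | 83% | 95% |
| 5% (14.5) | 21.2 | 50.8 | 71% | 91% |
| 10% (28.9) | 35.6 | 36.4 | 51% | 86% |
| 15% (43.4) | 50.1 | 21.9 | 30% | 81% |

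At L = 0, varying c from 0.95 to 0.99 moves the excluded share from 84% to 97%. If only 80% of completers are interviewed (assumed, c = 0.97), the share is about 93%, 77% and 60% at L = 0%, 5% and 10%.

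**Information left in the model.** If all 14 characteristics enter one model, seven sites need 6 parameters and the other 13 need at least one each, so at least 19. Failures per parameter are then 6.7/19 = 0.4, 21.2/19 = 1.1 and 35.6/19 = 1.9 at L = 0%, 5% and 10%.

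**Coding non-starters as non-adherent.** This keeps them in the model as far as adherence is concerned. All of them are failures by construction, so the adherence odds ratio partly restates the outcome definition. It does nothing for sexual behavior.

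**Treatment initiation as outcome.** If the same list is used for this secondary outcome, everyone with on-treatment data has initiated. The outcome does not vary and the model cannot be fitted.

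**The case against.** Several points on the other side are fair.

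- A reader might infer that adherence, like sexual behavior, is recorded only at treatment completion. The documents do not support that. Pickup dates in the medical record allow an adherence measure for anyone who started, including those lost later. It remains undefined for those who never started.
- A reader might infer that adherence is simply part of the outcome. The overlap is only partial. The second-interview section treats incomplete pickup, or no final test, as failure. The Analytical approach section requires both, and keeps participants with missed doses or pickups who return for a test, flagging them as non-adherent for descriptive use. A planned secondary analysis even reports how many cured participants were non-adherent. Sexual behavior does not enter the outcome definition at all.
- A reader might infer that the model discards nearly all failures. That requires fitting to complete cases and almost no loss between treatment completion and SVR12. The protocol states neither, and it expects that this population often does not return to clinic. Participants interviewed and then lost are failures with data.
- The protocol does not say that all 14 characteristics enter one model, or that this model covers all enrollees. It also plans per-protocol analyses, and it describes cascade losses separately. Such detail may sit in an analysis plan not shown here.

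These points limit the size of the problem and the wording of the claim. They do not remove the conflict: the text commits to evaluating two variables in an adjusted SVR12 model, and part of the population over which SVR12 is defined cannot have them.

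**Conclusion.** The point holds in this limited form. The listed adjusted model cannot be fitted meaningfully to all enrollees with sexual behavior and adherence in it. Fitted to those with both values, it excludes every never-starter and those lost before the second interview. That is about 91% of some 72 expected failures with no later loss, 71% with 5% and 51% with 10%, given 97% cure among those tested and complete-case fitting. The loss rates are assumptions, and above about 10% the excluded share falls below half (30% at 15%).

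If non-starters are coded as non-adherent instead, the adherence odds ratio is partly true by definition. Under either handling, adjusting for adherence blocks effects of housing, substance use or site that operate through it. This does not depend on the assumed rates.

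The primary SVR12 proportion comes from a model without predictors and is unaffected, as is the sample size. This is a fault in a supporting analysis, worth correcting because it determines which patients and which associations the adjusted odds ratios describe.

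**What to change.** State that the adjusted SVR12 model on all enrollees, and the similar model for treatment initiation, use only variables recorded at or before enrollment. Report adherence and sexual behavior descriptively, or in a separate model labelled as limited to participants who started treatment and have those data. For that separate model, say whether adherence comes from pickup dates or from the interview, and how missing values are handled.

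The cost is a sentence or two in the analysis section and no new data collection. The small downside is that there will be no all-enrollee adjusted odds ratio for these two variables.

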## Methods/design

### Setting

The study will be implemented at seven primary care clinics within CommUnityCare (CUC), Austin’s largest federally qualified health center (FQHC) network, which houses Austin’s Health Care for the Homeless program. The study sites were selected because of their focus on care for vulnerable, high-risk populations for HCV, including PEH and PWID. The study site locations include the following: (1) a full-spectrum primary care clinic located within the Austin Resource Center for the Homeless (ARCH) shelter (“the ARCH Clinic”); (2) a patient-centered medical home providing full-spectrum primary care for PEH as well as other medically complex and socially vulnerable patients following hospital discharge (“care connections”); (3) CUC’s dedicated clinic providing buprenorphine to individuals with opioid use disorder (medication-assisted therapy (MAT) clinic — “the MAT Clinic”); (4) a street medicine team brings care to PEH, meeting them at homeless campsites and under bridges (“the street team”); (5) a clinic located at Community First! Village (CFV), a permanent supportive housing community for individuals who were chronically homeless (“the CFV Clinic”); (6) a clinic located at Esperanza Community, a state-sanctioned encampment for PEH that is becoming a transformational shelter complex (“the Esperanza Clinic”); and (7) a full-spectrum primary care clinic space setup within Sunrise Church, providing care alongside the local mental health authority and other social service providers that partner with the Sunrise Homeless Navigation Center nonprofit that serves PEH in Austin (“Sunrise”).

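### Clinical site is a predictor in the adjusted SVR12 model and, on the natural reading, also its unstated GEE cluster; if so, the site odds ratio intervals are invalid

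*Protocol article*

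**What the plan says.** The Analytical approach section of the protocol article lists 14 patient characteristics to be examined by SVR12 status. The end of that list and the sentence after it read: "medical comorbidities, clinical site, and adherence to HCV treatment. These characteristics will also be evaluated after adjusting for covariates using a multivariable logistic regression model". The output is fixed too: "Reported outcomes will include adjusted odds ratios for SVR12 and their 95% confidence intervals". The next sentence gives the fitting method: "We will use GEE models to account for clustered data and correct for small sample size, as described above". What was described above is the method for the simple proportions, where "Bias-corrected GEE will be applied to account for a small sample size". Similar exploratory models are to follow for the secondary outcomes.

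Nowhere does the article name the cluster or a particular bias correction. It does not say that site leaves the predictor list when site is the cluster. The Setting section describes seven clinics, and Objective 2 gives each its own workflow.

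**The concern.** A GEE robust variance learns about uncertainty from how much the cluster totals of the score vary. If the cluster is the clinic and the model also has a free parameter for each clinic, the fit sets each clinic's total for its own parameter to zero. There is then no between-clinic variation left from which to estimate the variance of the site terms.

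At stake are the adjusted odds ratios for site and their 95% intervals. They would look much more precise than the data allow, and chance differences between clinics could be reported as established. A small-sample correction is meant to guard against an understated variance, but here the common ones either cannot be computed or do not help.

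**Working it through.** **Inputs from the protocol article.** Seven clinics (Setting). Site plus 13 other characteristics in the adjusted model; adjusted odds ratios with 95% intervals; GEE with a small-sample correction (Analytical approach). N = 289 and an expected SVR12 of 75% (Sample size justification).

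**The plan's own figure.** n = z²p(1 − p)/d² = 1.96² × 0.75 × 0.25 / 0.05² = 288.12, rounded up to 289. It reproduces, and 289 is the size used below.

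**Which cluster?** The clinic is the only grouping the design describes: workflows are developed clinic by clinic. A GEE small-sample correction addresses a small number of clusters, which fits seven clinics and not 289 patients. The Data collection section does record the primary care physician, but only as an extracted variable. The steps below are conditional on clinic as cluster.

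**Step 1, robust variance.** The sandwich is B M B, with B the inverse information and M = Σ UₖUₖ′, where Uₖ is the score total of clinic k. The estimating equation for the parameter of clinic k involves only patients in clinic k, so the fit makes that entry of Uₖ exactly zero. This holds under independence and exchangeable working correlation. The rows and columns of M for the site parameters are therefore zero. In a site-only model the robust SEs of the site log odds ratios are exactly 0. With other covariates, the only variance that reaches the site terms comes through their correlation with those covariates.

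**Step 2, small-sample correction.** Mancl-DeRouen and Kauermann-Carroll need the inverse (or inverse square root) of I − Hₖₖ, where Hₖₖ = Dₖ B Dₖ′ Vₖ⁻¹. Let dₖ be the site column of Dₖ. It is nonzero only in clinic k, so dₖ′Vₖ⁻¹Hₖₖ = dₖ′Vₖ⁻¹. Hence Hₖₖ has an eigenvalue of exactly 1 and I − Hₖₖ is singular. Numerically, its smallest eigenvalue was below 1e-13 in every clinic.

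**Step 3, size.** Simulation with 289 patients, SVR12 near 75%, no true site effect, and clinic sizes 80/60/50/40/25/20/14. The clinic sizes are an assumption; the article gives none.

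| Other covariates | Robust SE ÷ model-based SE, site terms | Coverage, robust 95% CI |
|---|---|---|
| 3 | 0.07 | 13% |
| 13 | 0.18 | 29% |
| 20 | 0.23 | 37% |

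Model-based SEs covered about 95%. Thirteen covariates means one term per listed characteristic; 20 allows for some with several categories. With no true site effect, coverage of 29% to 37% means that 63% to 71% of site intervals would wrongly exclude an odds ratio of 1.

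A second simulation, with near-equal clinics and a between-site SD of 0.4 on the logit scale, gave ratios of 0.18 and 0.24 and coverage of 25% and 37% with 12 and 20 covariates. Fay-Graubard could be computed there, but its median ratio was still only 0.26 with 20 covariates.

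**Step 4, one simulated data set with 12 covariates.** The first site term had a model-based SE of 0.531 and a robust SE of 0.129. As factors either side of the odds ratio, exp(1.96 × 0.531) = 2.83 against exp(1.96 × 0.129) = 1.29. The software's bias-reduced SEs for the six site terms ran from 0.19 to 3.63 under independence and from about 5,300 to 40,000 under exchangeable. This is numerical noise from inverting a singular matrix.

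**Step 5, with site only as the cluster.** The smallest eigenvalue of I − Hₖₖ is 0.54 to 0.86 with 0 to 20 covariates, so the correction is computable. In a 12-covariate example the bias-reduced SEs were about 0.20 to 0.52.

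**The case against.** The strongest reply is that the argument is conditional. The article does not name the cluster, and an analysis plan that is not shown may name it or drop site from the predictors. With provider as the cluster the degeneracy does not follow in general; it would remain only for a clinic with a single provider. That stands, and it is why the conclusion carries an if. It does not remove the point, because the text itself includes site in the model and applies clustered GEE to that model. No grouping other than the clinic is described.

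A reader might also infer several stronger things that the documents do not support.

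- *That the site SEs are practically zero.* This is true only with no or very few other covariates. With the planned list they are about a fifth of what they should be: badly wrong, but not zero.
- *That the plan's chosen correction cannot be computed.* No correction is chosen. Only the leverage-inverse ones fail; Fay-Graubard runs but leaves the site terms wrong.
- *That the trial's main result is at risk.* The primary proportion comes from a GEE with an intercept only.
- *That clinic comparison is a main aim.* The objectives and outcomes state no such comparison, and the outcomes are defined over all enrolled patients.
- *That adjusting for site spoils the housing or substance-use estimates because some clinics are defined by those features.* Within-site contrasts are a legitimate choice, and the article does not show how closely site and housing coincide.

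The false precision itself is confined to the site terms. Uncorrected robust intervals for patient-level covariates covered about 85% to 86% in simulation, with or without the site dummies. A leverage-inverse correction would still be undefined for the model as a whole.

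**Conclusion.** The point holds in conditional form. If the clinic is the GEE cluster, keeping clinical site as a predictor makes the robust intervals for the site odds ratios invalid. The zero site scores and the singular leverage matrices follow from algebra and do not depend on any assumed value. The size, about 0.2 times the correct SE and roughly 29% to 37% coverage with 13 to 20 covariates, rests on assumed clinic sizes, null covariates and no site effect; a different set of assumptions gave much the same answer.

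Severity is moderate. The defect sits in a secondary association model and would recur in the parallel exploratory models. It does not reach the primary SVR12 estimate.

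**What to change.** State the cluster unit. If it is the clinic:

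1. Remove clinical site from the predictors of the adjusted GEE model, so that site enters only as the cluster.
2. Report site differences separately, as SVR12 per clinic with Wilson or exact intervals. If adjusted site odds ratios are wanted, use an ordinary or Firth logistic model with site fixed effects, model-based SEs and no clustering on site.
3. Apply the same rule to the exploratory models for the secondary outcomes.

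The cost is a sentence or two in the analysis section. No new data are needed and the sample size does not change. What is given up is a single model that yields both site and patient-level odds ratios.
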